#### D.6.e. Assessing the cost-effectiveness of SODIS and estimating the social and economic impact of SODIS at household level.

We will use cost-effectiveness analysis to complete this objective. Cost-effectiveness analysis compares the net monetary costs of a health care intervention with a measure of clinical outcome or effectiveness such as mortality rates, life years saved or events averted.

The aim is to estimate the unit cost for averting 1 (one) episode of diarrhoea by SODIS. Further we will perform a cost description of the net savings for a household per episode of diarrhoea averted. Multiplying this figure with the preventive fraction obtained from Section D.e we will generate a specific measure of economical and social impact of the SODIS intervention.

Costs will be assessed from the perspectives of the household. Household costs for a diarrhoeal episodes will be determined through a convenient sample of 50 acute and 50 persistent/severe episodes. The following parameters of the participating households will be assessed: a.) *direct costs* for medication, care services, or transportation, and b.) *indirect costs* of caretaker-time lost from work from caring for the sick child, d.) *time lost* for transportation and e.) time lost for a visit (waiting and treatment). Daily logs will be maintained by the household to measure these indicators. We will use local estimates of hourly income for a economically productive women to estimate the hourly wage of the mothers/caretakers. Programme costs for the total episodes of diarrhoea averted by the intervention will include the following costs: a.) for community building/training for the use of SODIS, b.) for actual costs of the SODIS bottles and their handling (e.g. cleaning before distribution), c.) the distribution, and d.) replacement of broken bottles. Research costs will be excluded.

The economic costs of SODIS implementation will be summed over the two SODIS implementation periods (4-6 months (Appendix L)) of the two treatment arms of the trial. The bottles have an estimated life span of one year and will be treated as recurrent costs (i.e. they are not discounted). Financial costs derived from the programme budget as well as economic costs (including volunteer and donations) will be considered in order to establish cost-effectiveness ratio for the SODIS intervention. The number of episodes prevented by SODIS will be the difference in the observed episodes in the intervention households and the control households from Section D.6.d.)

We will finally conduct a sensitivity analysis computing cost-effectiveness ratios of the SODIS implementation for different replacement costs of SODIS bottles (doubled and tripled per year, and discount rates varied from 3% and 10% which is in agreement with recent economic evaluation practice in low income countries (The World Bank 1993). The net cost per episode prevented will then be calculated by dividing the cost of SODIS implementation by the diarrhoeal episodes averted (cost-effectiveness ratio).

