- Evaluate the hypothesis that SODIS reduces the incidence of gastrointestinal illness in 660 children under the age of five years in rural Bolivia that are randomly selected from 22 villages ;
- Define, through an extensive microbiologic testing component, the baseline rates of pathogen-specific diarrheal illnesses and the pathogens responsible for the differences in diarrheal illness between active and control groups;
- Document the actual use and acceptance of SODIS by participants in the study;
- Assess the cost-effectiveness of SODIS and the social and economic impact of SODIS at household level;
- Examine through mathematical disease modelling the effects of the presence of multiple transmission pathways within a village on the preventable fraction estimate due to the introduction of SODIS.

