#### D.6.d. Estimation of diarrheal disease preventive fraction of child-diarrheal illness.

Applying the definition of Last, community effectiveness is defined in this setting as the impact of the SODIS intervention on the overall incidence rate of child diarrhea in the community (Last 1995). It can be expressed in two ways:

- i.) The relative risk (the ratio of the risk of diarrhea in the intervention group to that in the control group). With this ratio the community protective effect ( $CPE = (1-RR) \times 100$ ) can be obtained which expresses the percent reduction in the overall diarrheal incidence rate as a result of the SODIS intervention.
- ii) The number of diarrheal illnesses averted as a result of the intervention (attributable risk) is measured by the difference in incidence density rates between the two study groups. To obtain an absolute number of diarrheal illnesses prevented by the use of SODIS, we multiply the attributable risk with the number of diarrheal cases obtained from the cross-sectional study. (In this calculation we assume that the results from the 22 cross-sectional studies represent the frequency of diarrheal illness in the general population).

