## D.8. Sample size calculation

Sample size calculations were designed for the trial to detect a 33% absolute reduction in the annual diarrheal incidence rate in children below the age of 5 in SODIS users compared to non-users. We consider a reduction of the annual incidence of 5 to 3.33 episodes per child <5 as of significant public health importance (Bern et al. 1992). This absolute rate reduction (1.67 episodes/child/year) is even lower than what was found in the Kenyan SODIS trials (2.1 epi/ch/yr)(Conroy et al. 1999). Conroy observed 2546 diarrhoeal episodes among a total of 4382 fortnight observation periods (58.1%) in the control group (172 children). A total of 2210 episodes among 4323 observations (48.8%) were found in the intervention group (174 children) resulting in their report of a 9.3% reduction of diarrhoea in children below 6 years. By considering 26 repeated measurements of fortnight periods an approximation of the annual incidence, the Conroy findings suggest an average annual reduction of 2.1 episodes/child/year for a child in the control *versus* intervention group (14.6 *versus* 12.7 epi/ch/yr). The magnitude of diarrhea reduction we have powered the study to detect compares favorably to the achievements of other well designed interventions that influenced national diarrheal disease control programs elsewhere in developing countries (Huttly et al. 1997, Stanton and Clemens 1987).

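### D.6.e multiplies the household saving per averted episode by the preventive fraction, which gives a figure with no time or household unit; the multiplier should be the incidence-rate difference

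*Protocol*

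**What the plan says.** Section A makes the economic question a specific aim: "Assess the cost-effectiveness of SODIS and the social and economic impact of SODIS at household level". D.6.e sets out two calculations.

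- **Cost per episode averted.** The cost of implementation is divided by the episodes averted, and for that count the section says: "The number of episodes prevented by SODIS will be the difference in the observed episodes in the intervention households and the control households".
- **Household impact measure.** It starts from a saving per averted episode: "Further we will perform a cost description of the net savings for a household per episode of diarrhoea averted". The next sentence gives the rule for turning that saving into an impact: "Multiplying this figure with the preventive fraction obtained from Section D.e we will generate a specific measure of economical and social impact".

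No section is labelled D.e. The section with preventive fraction in its title is D.6.d, which defines two separate quantities. Item (i) is the community protective effect, (1-RR) x 100, which "expresses the percent reduction in the overall diarrheal incidence rate as a result of the SODIS intervention". Item (ii) is an absolute measure: "The number of diarrheal illnesses averted as a result of the intervention (attributable risk) is measured by the difference in incidence density rates". The Project Summary uses the term preventive fraction for the share of all-cause child diarrhea attributable to SODIS, that is, as a proportion.

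**The concern.** A saving per averted episode becomes a total only when it is multiplied by a number or rate of averted episodes. Multiplying it by a proportion applies the effect a second time and leaves out how often children have diarrhea. The result is not a saving per child, per household or per year. Two villages with the same relative effect would get the same figure even if one had several times as much diarrhea to prevent.

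The sentence is also loose enough to be carried out in more than one way. D.6.d offers a percentage, the proportion behind it and a rate difference, and the cross-reference does not settle which is meant. What is at stake is the household impact figure reported under a specific aim.

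**Working it through.** **Inputs**

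- Control and intervention rates, D.8: "We consider a reduction of the annual incidence of 5 to 3.33 episodes per child <5 as of significant public health importance". Table 1 writes the lower rate as 3.333, so R0 = 5 and R1 = 3.333 episodes per child-year.
- Range of background incidence, C.3 and D.8: 4 to 5 episodes per child-year.
- Saving per averted episode: S. The protocol gives no amount, so results are left as multiples of S.

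**Reproducing the protocol's figures**

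- Relative reduction: PF = 1 - R1/R0 = 1 - 3.333/5 = 0.333, the 33% stated in D.8.
- Absolute reduction: R0 - R1 = 5 - 3.333 = 1.667, the 1.67 episodes per child-year stated in D.8.

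**Written rule against saving per child-year**

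- D.6.e as written, fraction as a proportion: S x PF = 0.333 x S.
- Saving per averted episode times episodes averted: S x (R0 - R1) = 1.667 x S per child-year.
- Ratio: (R0 - R1)/PF = R0, because R0 - R1 = R0 x PF. It does not depend on S or on the effect size. It is 5.0 at R0 = 5, 4.5 at R0 = 4.5 and 4.0 at R0 = 4.

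**Fraction entered as the percentage in D.6.d(i)**

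- At R0 = 5: 33.3 x S against 1.667 x S, so 33.3/1.667 = 20 times too large.
- At R0 = 4 with the same relative effect, episodes averted are 4 x 0.333 = 1.333, so 33.3/1.333 = 25 times too large.

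**Insensitivity to incidence**

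Take two villages with PF = 1/3, one at 2 and one at 10 episodes per child-year (illustrative rates). Episodes averted are 0.67 and 3.33 per child-year, a five-fold difference. The written rule gives 0.333 x S in both.

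**Units**

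S is money per averted episode. PF is averted episodes divided by episodes expected without SODIS. Their product is money per expected episode. The rate difference is averted episodes per child-year, so S times the rate difference is money per child-year. For a household with n children under five at the same rates it is n x 1.667 x S per year, for example 3.33 x S with two. C.1 reports that 54.3% of pilot families had more than one child under five, so the unit has to be stated.

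**The case against.** The strongest reply is that the wording is loose and the calculation is not really wrong. D.6.e never writes (1-RR). D.6.d uses preventive fraction only in its title and places the number averted under that title. Later in D.6.e the episodes prevented are taken from D.6.d. The authors may have meant the D.6.d result in general. This is possible, but it does not rescue the sentence. The text names a fraction, the Project Summary uses the term as a share, and the reference points to no section. Someone following it could report 0.333 x S, 1.67 x S or 33.3 x S.

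A second reply is that five is not the size of an error in the document. This stands. D.6.e gives no period, and the ratio is simply the control rate in whatever time unit is chosen: 5 per year is 5/12 = 0.42 per month, or 10 over two years. The direction also depends on whether a proportion or a percentage is entered. A reader might infer that the plan understates household impact about five-fold, but the documents support that only per child-year and only for a proportion.

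A reader might also infer that SODIS would look uneconomic, by setting the product against the annual cost per family of $1.20 to $2.10 quoted in the introduction to the revised application. The documents do not support this. That range is a preliminary estimate from earlier work, and no section plans the comparison. It would set a per-child saving against a per-family cost. The saving is also described as net without saying of what, so if SODIS cost is already deducted the comparison would count it twice.

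Finally, the cost per episode averted does not use this sentence. That is correct and limits the consequence.

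**Conclusion.** The point holds in a limited form. Followed as written, D.6.e yields a saving per episode expected without SODIS, which is not a household impact over any period and is the same at every baseline incidence. Per child-year at the design rates, the written product is 0.333 x S where the saving is 1.67 x S. The factor is the control incidence, 4 to 5 on the protocol's range, assuming the fraction is entered as a proportion. Entered as a percentage, the product is 20 to 25 times too large. These sizes rest on the planning rates and on choosing the child-year as the unit. That the product lacks a time unit and an incidence term rests on neither.

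The consequence is confined to one secondary economic measure, though it serves a stated aim. The primary analysis, the sample size and the cost per episode averted do not change.

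**What to change.** In D.6.e, replace the multiplier with the episodes averted per child-year, meaning the incidence-rate difference defined in D.6.d(ii). This agrees with the difference in episodes already used for the cost-effectiveness ratio. Suggested wording: the net household saving per episode averted will be multiplied by the difference in incidence rates between control and intervention groups (Section D.6.d, item ii), giving the saving per child-year; where a household figure is reported, it will be scaled by the number of children under five. Correct the reference from Section D.e to D.6.d.

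The cost is one sentence and one cross-reference. The per-episode saving and both incidence rates are already to be collected, so no new data are needed.

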## D. Research Design and Methods

### D.1. Overview of the design

The principal aim of the proposed study is to evaluate the ability of a simple, low-cost, home-based water treatment method based on solar disinfection to reduce gastrointestinal illness among children less than 5 years of age in rural Bolivian communities. To achieve this objective we will conduct a pair-matched, cluster-randomized controlled trial following equal numbers of children in each of 22 villages (Appendix L). The intervention to be tested is a method called SODIS (Solar Disinfection) which makes use of the synergistic effects of solar radiation and thermal heating from sunlight. The SODIS Program, by design, disseminates the intervention to whole communities, rather than to individual households or single individuals. The major steps in the randomization process are:

1. 22 villages (from a total of 60 possible villages) will be selected for enrollment from the Totora District;
2. each village will be paired with another village with a similar incidence of baseline diarrhea, as suggested by the reviewer previously;
3. within each pair of villages, one village will be randomly selected for the “treatment” arm and one village for the “control” arm.
4. within each village all families will receive the SODIS intervention. A random sample of 30 children under 5 years of age will be enrolled in the study (total of 330 children in each arm of the study, 660 children total for the study). In families with multiple children the youngest child will be enrolled.

Please note that study introduces no delay into the receipt of SODIS by the control villages because control arm communities will receive the SODIS intervention at the end of the trial according to the scheduled implementation plans of the SODIS Program.

The 660 children (all <5 years old at enrollment), will be followed and monitored for the occurrence of diarrheal diseases over a period of 12 months. Data on diarrheal illness will be obtained from daily morbidity diaries kept by mothers/caretakers (\*) and through weekly home visits by our project staff. Participating mothers/caretakers of participating children will be interviewed at baseline and repeatedly during the trial with regard to current water management, behavioral and environmental exposures of their child in the household and the community surroundings.

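### The cost-effectiveness sensitivity analysis varies only cost inputs and leaves episodes averted at its point estimate, so its range omits a material source of uncertainty

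*Protocol*

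**What the plan says.** Protocol Section D.6.e obtains the net cost per episode by "dividing the cost of SODIS implementation by the diarrhoeal episodes averted (cost-effectiveness ratio"). Its denominator is a single quantity: "The number of episodes prevented by SODIS will be the difference in the observed episodes in the intervention households and the control households", taken from Section D.6.d. Section D.6.d defines it as the difference in incidence density between the arms and gives no interval.

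The sensitivity analysis names two inputs. It consists of "computing cost-effectiveness ratios of the SODIS implementation for different replacement costs of SODIS bottles (doubled and tripled per year, and discount rates varied" between 3% and 10%. Nothing else is listed.

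Three further statements bear on the discount rate:

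- Bottles, with a life of one year, "will be treated as recurrent costs (i.e. they are not discounted").
- Economic costs are "summed over the two SODIS implementation periods (4-6 months (Appendix L)) of the two treatment arms of the trial". Section D.1 adds that "control arm communities will receive the SODIS intervention at the end of the trial".
- Programme costs include items other than bottles, among them those "for community building/training for the use of SODIS" and distribution.

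No cost item is named as the one to which the discount rate applies.

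**The concern.** A cost per episode averted is only as certain as both of its parts. Here the denominator is the effect that the trial sets out to estimate, from 11 villages per arm, and it carries sampling error. A sensitivity analysis that moves only the numerator gives a range conditional on the effect being known exactly. If the estimated effect is positive but weak, the plan still yields a finite ratio with a bounded range, although the data may be compatible with no episodes averted.

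Cost-effectiveness is one of the Specific Aims. The introduction to the revised application says that results go to the programme management and the Bolivian government for rapid decisions. The uncertainty left out is whether SODIS works under programme conditions, which is the reason given for running the trial.

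**Working it through.** **Inputs**
- Section D.8: rates R0 = 5 and R1 = 3.33 (taken as 3.333, difference 1.667) episodes per child-year; z = 1.96 and 0.84; 11 villages per arm; 30 children per village.
- Section D.8: k = 0.2 in the final calculation, and 0.3 or lower as the stated conservative assumption.
- Assumed here: full follow-up (y = 30 person-years per village), no gain from pair-matching, and a fixed numerator.

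**The plan's own figure.** The formula in Section D.8 with y = 10 and k = 0.2:

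c = 2 + (1.96 + 0.84)² × {8.333/10 + 0.04 × (25 + 11.11)} / 1.667² = 2 + 7.84 × 2.278 / 2.778 = 8.43

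This rounds up to the stated 9 villages per arm, so the variance terms are read correctly.

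**Precision of the denominator.** The same terms give SE = √[{(R0 + R1)/y + k²(R0² + R1²)} / 11] and a 95% interval of difference ± 1.96 × SE. With the numerator fixed, the ratio at each limit is (point difference / limit) times its point value.

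- k = 0.1: SE = √(0.639/11) = 0.241; interval 1.19 to 2.14; ratio × 0.78 to × 1.40 (1.8-fold).
- k = 0.2: SE = √(1.722/11) = 0.396; interval 0.89 to 2.44; ratio × 0.68 to × 1.87 (2.7-fold).
- k = 0.3: SE = √(3.528/11) = 0.566; interval 0.56 to 2.78; ratio × 0.60 to × 2.99 (5.0-fold).

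**Smaller effects that Section D.8 itself considers**
- 16% reduction (5 to 4.2) at k = 0.12, the pairing named there: SE 0.289; interval 0.23 to 1.37; ratio × 0.59 to × 3.43.
- 16% reduction at k = 0.2: SE 0.428; interval −0.04 to 1.64. It includes zero, so the ratio has no finite upper limit.
- 20% reduction (5 to 4, a row of Table 2) at k = 0.3: SE 0.602; interval −0.18 to 2.18. Again no finite upper limit.

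**Bottle cost.** If bottles make up a share s of total cost, tripling their cost multiplies the ratio by 1 + 2s. The documents do not give s. The multiplier is 1.2 at s = 10%, 2.0 at 50% and 3.0 at 100%. Set against k = 0.2, tripling exceeds the upper multiplier (1.87) once s passes about 43%, and exceeds the full 2.7-fold spread once s passes about 87%. For scale, the family cost range by bottle lifespan in the introduction, $1.20 to $2.10, is 1.75-fold.

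**Discount rate.** Suppose half the cost falls one year later. Total cost is 0.5 + 0.5/1.03 = 0.985 at 3% and 0.5 + 0.5/1.10 = 0.955 at 10%, a fall of 3.1%. If the delay is two years, the figures are 0.971 and 0.913, a fall of 6.0%. The half share and the delays are assumptions.

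**The case against.** The strongest reply is that this is an omission. Section D.6.e does not say that its two inputs are exhaustive, and Sections D.5 and D.9 plan a cluster-adjusted effect estimate with robust variance. An interval for the ratio could be left to a later analysis plan, and nothing says that the ratio would be published without the trial's confidence interval. That is fair as to reporting. It does not fully answer the point, because the protocol itself specifies the sensitivity analysis and chooses its inputs, and every input chosen is on the cost side.

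A second reply is that the intervals above ignore pair-matching on eight-week baseline diarrhoea and covariate adjustment, both meant to reduce variance. This stands, and the multipliers should be read as unmatched planning values. In the other direction, they assume no loss to follow-up and use 1.96 rather than a t quantile.

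A reader might infer two stronger things that the documents do not support. The first is that the discount rate has nothing to act on. Only bottles are exempted. Training and distribution are costed too, and the control arm's implementation follows the 12-month trial, so costs span more than a year. The effect looks small, about 3% to 6% under the assumptions shown, but it is not zero. What remains is that the discounted items are not named.

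The second is that the effect is the largest uncertainty in the ratio. The bottle share of programme cost is not given, so this cannot be shown. The family cost range suggests that at least $0.90 of $2.10, about 43%, depends on bottles at the short lifespan. That is family rather than programme cost, but it leaves the ranking open.

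**Conclusion.** The point holds. As written, the sensitivity analysis leaves the trial's own estimate at its point value, and the spread it omits is material: 2.7-fold at k = 0.2 and 5.0-fold at k = 0.3 for the design effect, and without a finite upper limit for some smaller effects. These sizes rest on the protocol's variance formula without matching, full follow-up and a fixed numerator. They do not establish that the omitted source outweighs bottle cost. The discount rate needs a stated target, which is a matter of clarification. The point concerns a secondary aim and does not touch the design or the primary inference, but the change is worth making because the ratio is meant to inform programme decisions.

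**What to change.** In Section D.6.e, add to the sensitivity analysis the cost-effectiveness ratio recomputed at both cluster-adjusted 95% limits of the rate difference. State that if the interval includes no effect, the ratio has no finite upper limit and will be reported so. Section D.9's regression returns rate ratios, so say how the limits of the difference are obtained, for example from the village-level rates.

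In the same section, name the cost items to which the 3% to 10% rate applies, such as training and the control arm's later implementation period, since bottles are excluded.

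This needs no new data: a few lines of analysis, and a wider reported range. Resampling village pairs together with their costs would be fuller, but it needs village-level costing that the protocol does not describe, so it is not required here.
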